### Power and Sample Size

We used the General Linear Mixed Model Power and Sample Size (GLIMMPSE) application to estimate the sample size needed for this study using the approach for longitudinal data (29). We calculated the sample size needed to detect a 40% lower change in use across time among the GRIT versus active control arm for both outcomes, as the Strengthening Families Program cited 50% reductions (30). In addition, we judged that a 40% reduction in initiation rate would be needed for a clinically meaningful effect. Given that exposure to four or more ACEs is associated with a two-to three-fold increase in early initiation (i.e., before age 14) of alcohol and cannabis use and national high school samples report initiation of alcohol before 13 to be 15% and cannabis to 5%, we conservatively assumed a 20% initiation for alcohol and 8% for cannabis for our high-risk study population (31–34). We also accounted for 20% attrition during the 14-month follow-up period and a variance inflation factor of 1.4 to accommodate the mediation analysis. Under these assumptions, a sample size of 105 dyads per arm (total N = 210 dyads) would be needed to provide 80% power at a nominal alpha of 0.025 for each outcome (adjusted for multiplicity to achieve an overall alpha of 0.05 for both outcomes). Previous research, such as the Support to Reunite, Involve, and Value Each Other (STRIVE) study and its adaptation, STRIVE +, has informed the sample size for this study. STRIVE evaluated a 5-session dyadic psychoeducational intervention with youth experiencing homelessness, enrolling 151 youth with a retention rate of 77% at a follow-up (3, 6, and 12 months) (35). STRIVE demonstrated efficacy in significantly reducing substance use, sexual risk, alcohol use, and illicit drug use over 12 months compared to the control condition. Given these findings, family based-interventions like GRIT may similarly reduce substance use and improve overall health and well-being. The findings from STRIVE+ further informed the design of our study, particularly highlighting the need for additional sessions and booster sessions. In STRIVE+, parents requested more sessions to practice newly acquired skills, as they experienced difficulties with familial connection. Based on STRIVE’s successful retention and outcomes, we believe that a sample size of 210 dyads (N=420) for the GRIT study is reasonable, as it allows us to detect meaningful differences in substance use outcomes between the GRIT intervention and the control group.

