### Outcomes

The primary outcome is adolescent initiation of regular alcohol and cannabis use. Alcohol and cannabis use will be measured using items from the CDC Youth Risk Behavior Survey (YRBS) and the frequency of use will be assessed using the Timeline Followback (TLFB) method. Regular alcohol or cannabis use is defined as at least weekly use. Secondary outcomes include anthropometrics, heart rate variability, emotional regulation, psychological health, health behaviors, and family functioning. Outcomes will be measured at baseline, post-intervention (2 months), 6 months post-intervention, and 12 months post-intervention.

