### Data Analysis Plan

Baseline characteristics will be summarized using descriptive statistics to assess group balance. Primary analyses will follow the intention-to-treat principle, with all randomized participants included. Changes in adolescent alcohol and cannabis use will be compared between study arms using generalized linear mixed models (GLMMs) to account for within-subject correlation over time. Alcohol and cannabis use will be dichotomized as no or occasional use versus regular use (weekly or more) to evaluate the intervention’s effect on preventing initiation of regular substance use. Statistical significance will be assessed using two-sided tests with an alpha level of 0.05.

Multilevel mediation analyses will be conducted to examine mechanisms underlying intervention effects, with youth and caregiver emotional regulation specified as primary mediators. Additional exploratory mediators will include heart rate variability, psychological and cognitive flexibility, youth health behaviors (HRV biofeedback practice, sleep, nutrition, physical activity), and environmental factors (parental monitoring, family functioning, and caregiver substance use). Indirect and direct effects will be estimated using residual-based bootstrap methods to generate 95% confidence intervals. Sex differences will be evaluated in secondary analyses by including a sex-by-intervention interaction term.

Our primary analysis will be performed using mixed effects analysis, which provides unbiased estimates when missing data is missing at random (MAR). We will also consider multiple imputations to handle missingness using the Rubin method implemented in R package mice (53,54).

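### The Data Analysis Plan sets two-sided 0.05 without saying whether that is per outcome or overall, while the sample size rests on 0.025 for each of two primary outcomes

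*Protocol article*

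**What the plan says.** Three sections of the Protocol article bear on this.

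- **Power and Sample Size.** The trial is sized for "80% power at a nominal alpha of 0.025 for each outcome", and the reason follows in parentheses: "adjusted for multiplicity to achieve an overall alpha of 0.05 for both outcomes". The target effect is to "detect a 40% lower change in use across time among the GRIT versus active control arm for both outcomes". Separate control rates are assumed: 20% for alcohol and 8% for cannabis.
- **Outcomes.** The wording is singular: "The primary outcome is adolescent initiation of regular alcohol and cannabis use". No composite of the two substances is defined.
- **Data Analysis Plan.** "Changes in adolescent alcohol and cannabis use will be compared between study arms using generalized linear mixed models (GLMMs"), each after a split into regular and non-regular use. The paragraph closes with: "Statistical significance will be assessed using two-sided tests with an alpha level of 0.05".

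The Data Analysis Plan mentions no division of alpha, no testing order, and no statement that 0.05 is the level for the pair. No other section gives a multiplicity rule for the analysis.

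**The concern.** The sponsor decided at the design stage that two outcomes need an adjustment and paid for it in the sample size. The section an analyst would follow does not carry that decision forward. Its 0.05 comes directly after the description of the alcohol and cannabis models and is attached to the tests themselves, so the natural reading is 0.05 for each.

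Two things are at stake. First, on that reading the trial loses the error control that its sample-size section claims. Second, the primary conclusion becomes undetermined over a range of results. With p = 0.03 for one outcome, Power and Sample Size makes it a failure and the plain reading of the Data Analysis Plan makes it a success. That choice should be closed before anyone sees results.

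This is not a detail left to a statistical analysis plan that is not shown. The article does state a level for the analysis, and that level does not visibly match its own design.

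**Working it through.** **Inputs**

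- Per-outcome alpha 0.025 and overall alpha 0.05: Power and Sample Size.
- Two-sided tests at 0.05: Data Analysis Plan.
- Number of primary tests: two. Power and Sample Size speaks of each outcome and of both outcomes, with separate rates, and no composite is defined.
- Correlation ρ between the two test statistics: not given. It is assumed here, from 0 to 0.9.
- Success rule: not written. Success on either outcome is inferred, because dividing alpha serves a purpose only if one outcome alone can support a claim.

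**Step 1. Reproduce the stated figure**

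Bonferroni sum: 0.025 + 0.025 = 0.05, as stated. If the tests are independent, the error is 1 − (1 − 0.025)² = 0.0494. The design rule therefore holds the overall level at or below 5%.

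**Step 2. Each outcome at two-sided 0.05, either one counting as success**

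- Upper bound: 0.05 + 0.05 = 0.10.
- Independent tests: 1 − (1 − 0.05)² = 1 − 0.9025 = 0.0975.
- Correlated tests: for Z₁ and Z₂ standard bivariate normal with correlation ρ, the family-wise error is 1 − P(|Z₁| < c and |Z₂| < c). Here c = 1.960 for alpha 0.05 and c = 2.241 for alpha 0.025.

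| Assumed ρ | Each at 0.05 | Each at 0.025 |
|---|---|---|
| 0 | 9.75% | 4.94% |
| 0.3 | 9.51% | 4.84% |
| 0.5 | 9.07% | 4.65% |
| 0.7 | 8.35% (8.345%) | 4.30% |
| 0.9 | 7.04% | 3.62% |

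**Step 3. If success on both outcomes were required**

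The chance of two false positives cannot exceed the chance of one, so with each test at 0.05 the error is at most 5%. The inflation in Step 2 therefore depends on the either-outcome rule.

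**Step 4. Effect on the sample size**

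The stated 105 dyads per arm was computed at 0.025 per outcome. Bringing the Data Analysis Plan to that level leaves the stated N as it is.

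**The case against.** The strongest reply is that the sections may agree. Power and Sample Size contains both numbers, 0.025 per outcome and 0.05 overall, and the Data Analysis Plan sentence does not say per outcome. Read as the overall level, its 0.05 matches the design. This reading is possible, so a reader who infers that the two sections cannot both be followed goes further than the text allows. What remains is that the sentence is not worded as an overall level, and even if it were, it would not say how the 0.05 is to be divided.

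A second reply is that no section says success on either substance is enough. That is correct. The Outcomes section is worded in the singular, and a rule requiring both would control the error at 0.05 per test. The alpha split points the other way, but it supports an inference and not a quotation.

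A third reply is that a headline of nearly 10% uses the independence value. A reader might take 9.75% as the expected inflation. The article does not support that, since it gives no correlation, and use of the two substances is plausibly positively correlated. All the figures also rest on a normal approximation. With 105 dyads, 20% attrition and an 8% cannabis rate, about 105 × 0.80 × 0.08 = 6.7 control-arm events are expected among completers, so the true test level may differ somewhat from nominal.

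Finally, the published 0.025 already limits a later choice of threshold, because anyone using 0.05 per outcome would contradict the design. It limits the choice but does not settle it: no section ranks one statement above the other.

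**Conclusion.** The point holds as an unresolved mismatch between the level used for design and the level stated for analysis. It is not a proven contradiction. On the plain reading of the Data Analysis Plan, and if success on either outcome counts, the family-wise error is 9.75% under independence and about 8.3% to 9.5% at assumed correlations of 0.7 to 0.3, against the intended 5%. It still exceeds 5% at an assumed correlation of 0.9. If 0.05 is meant as the overall level, or if both outcomes must succeed, there is no inflation, but the article says neither. The threshold decides the primary claim, so it should be settled in the text before results are known.

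**What to change.** Replace the significance sentence in the Data Analysis Plan with:

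> *Each of the two primary outcomes (regular alcohol use, regular cannabis use) is tested at two-sided 0.025, for an overall alpha of 0.05, with 97.5% confidence intervals.*

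This restates the rule already in Power and Sample Size, makes its sidedness explicit and leaves N unchanged. The cost is a stricter threshold than the Data Analysis Plan now gives: a p-value between 0.025 and 0.05 on a primary outcome would no longer count as significant.

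Holm's procedure at overall two-sided 0.05 is an acceptable alternative. It starts at the same 0.025 and is never less powerful than the plain split. Its second step tests at 0.05, however, so the second outcome could be declared significant while its 97.5% interval includes no effect. If Holm is chosen, the 97.5% intervals must not be presented as matching the second-step decision.

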
### Retention Strategies

#### Incentives.

Dyads receive a monetary incentive for completing their data collection measures. Both the youth and caregiver are compensated with a $50 Amazon e-gift card for completing each assessment at baseline, post-intervention, 6-month post-intervention, and 12-month post-intervention. If dyads are unable to complete an in-person data collection where we conduct the HRV assessment and collect anthropometrics, but at least complete the online surveys, they receive a $25 Amazon e-gift card. Additionally, a monthly competition is held for dyads randomized to the GRIT arm, in which individuals and dyads with the highest average of minutes practiced using their Inner Balance trainer receive a bonus $10 Amazon e-gift card. This bonus reward is to encourage engagement in the self-regulation techniques using biofeedback outside of the intervention session time.

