### Intervention Group: Garnering Resilience in Traumatized Youth and Families

Participants randomized to the intervention group will receive GRIT, a six-session psychoeducational health coaching intervention designed to promote self-regulation and healthy habit development. GRIT is delivered to adolescent–caregiver dyads using a trauma-informed, coaching-based approach that emphasizes responsive communication and skill practice. Adolescents and caregivers may attend sessions jointly or individually, as needed.

To support skill acquisition and ongoing practice, each dyad is provided with an Inner Balance Trainer made by HeartMath^®^ and instructed in heart rate variability biofeedback (HRV-BF) practice. CHWs introduce and reinforce HRV-BF throughout the intervention, and regular practice using HRV-BF is incentivized through monthly competitions based on the total number of minutes practiced. Participants retain the device following the study’s completion to support continued use.

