### Emotional Regulation

Difficulties in Emotional Regulation- Short Form (DERS-SF) is used to collect data on emotional regulation abilities for both youth and caregivers. The DERS-SF is an 18-item self-report, an abbreviated version of the original 36-item questionnaire (49). Emotional regulation is measured on 6 subscales: strategies, non-acceptance, impulse, goals, awareness, and clarity. Total scores range from 18 to 90, with higher total scores on the DERS-SF indicating greater difficulties in emotion regulation.

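### HRV-biofeedback practice can occur only in the GRIT arm, so it belongs in a within-GRIT dose-response, not in the two-arm mediation; the bootstrap also needs a form suited to a binary outcome

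*Protocol article*

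**What the plan says.** All references are to the protocol article.

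- **Mediators.** The Data Analysis Plan sets up multilevel mediation analyses "with youth and caregiver emotional regulation specified as primary mediators". It then adds a second tier: "Additional exploratory mediators will include heart rate variability, psychological and cognitive flexibility", followed by "youth health behaviors (HRV biofeedback practice, sleep, nutrition, physical activity"), and a group of environmental factors. Practice thus stands in the same list as sleep, nutrition and physical activity.
- **Where practice can happen.** The section on the GRIT intervention group, and no other, states that "each dyad is provided with an Inner Balance Trainer" and describes instruction in its use. Under Incentives, "a monthly competition is held for dyads randomized to the GRIT arm". The Sampling section asks for willingness to install the app only in case of assignment to GRIT. The Introduction says that the control condition was built without self-regulation content. Practical Challenges and Limitations again ties the practice competitions to the GRIT group.
- **Intervals.** One method is named for every mediator: "Indirect and direct effects will be estimated using residual-based bootstrap methods to generate 95% confidence intervals".
- **Outcome.** For the comparison of arms, "Alcohol and cannabis use will be dichotomized as no or occasional use versus regular use (weekly or more"). The outcome scale for the mediation models is not restated.
- **Allowance for mediation.** Power and Sample Size includes a variance inflation factor (VIF) of 1.4 on account of the mediation analysis.

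**The concern.** A two-arm mediation analysis asks how much of the effect of assignment passes through a variable that assignment shifts. Sleep, nutrition and emotional regulation vary in both arms and can be studied in this way. Biofeedback practice cannot vary among controls. It is the dose of one component of GRIT, and entering it as a mediator joins a path that is true by definition (GRIT youth practise, controls do not) to a slope that reflects who chose to practise.

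The Discussion presents biofeedback within family psychoeducation as the novel element of this trial. A reported effect of GRIT through practice would readily be taken as evidence that biofeedback is the mechanism. More motivated or better supported families may both practise more and have youth who use less, and randomisation gives no protection against that.

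The interval method is a second, smaller matter. A residual bootstrap in its plain form is made for continuous outcomes, and the plan dichotomises use.

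**Working it through.** **1. What the data can tell about practice.** Let A be arm (0 control, 1 GRIT), M practice and Y regular use. By design M = 0 for all controls.

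- A to M: the difference in mean practice equals the GRIT mean. It cannot be zero unless nobody in GRIT practises, so it tests nothing.
- M to Y given A: controls all sit at M = 0 and fix only the intercept. In a model with A and M, the coefficient of M is exactly the slope within GRIT, which is not randomised.
- Indirect effect evaluated under control: this needs the outcomes of control youth who practise. There are none, so it cannot be estimated from these data.
- Indirect effect evaluated under GRIT: this compares GRIT youth at their actual practice with GRIT youth at zero practice. It needs GRIT youth who practise little or not at all (or extrapolation by the model), and no unmeasured common cause of practice and use.

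**2. The plan's own figure.** The VIF of 1.4 is an input to the sample size and is not derived in the article. It corresponds to R² = 1 − 1/1.4 = 0.286 between arm and mediator, a correlation of √0.286 = 0.535.

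**3. The VIF for a mediator that exists in one arm.** Under 1:1 allocation, with GRIT mean μ and standard deviation σ, the between-arm variance of M is μ²/4 and the average within-arm variance is σ²/2. Hence

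R² = (μ²/4) / (μ²/4 + σ²/2)

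VIF = 1/(1 − R²) = 1 + μ²/(2σ²) = 1 + 1/(2·CV²), with CV = σ/μ.

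The documents give no CV, so a range is shown:

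| Assumed CV | VIF | Against 1.4 |
|---|---|---|
| 0.25 | 1 + 1/0.125 = 9.0 | above |
| 0.5 | 1 + 1/0.5 = 3.0 | above |
| 1 | 1 + 1/2 = 1.5 | above |
| 1.5 | 1 + 1/4.5 = 1.22 | within |

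The allowance is met when 2·CV² ≥ 1/0.4 = 2.5, that is, when CV ≥ √1.25 = 1.12.

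**4. The plain residual bootstrap with a 0/1 outcome.** The method adds a residual drawn from one youth to the fitted value of another. Take the planning risk of 20% in controls and 12% in GRIT (40% lower). A fitted value of 0.20 plus the residual of a GRIT non-user gives 0.20 + (0 − 0.12) = 0.08. With the residual of a GRIT user it gives 0.20 + (1 − 0.12) = 1.08. Neither is 0 or 1, so a logistic model cannot be refitted to them as a binary outcome.

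**5. Does this spoil the intervals?** A single-level simulation was used: 84 youth per arm (105 × 0.8), a binary outcome with 20% risk at mediator value zero, a linear outcome model with the product of coefficients, 400 trials and 300 resamples. The effect sizes and the practice distribution (CV 1) are assumptions.

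| Mediator | Bootstrap | Coverage of 95% interval | Mean width |
|---|---|---|---|
| Continuous, both arms | residual | 94.0% | 0.080 |
| Continuous, both arms | case | 93.2% | 0.081 |
| Practice, GRIT only | residual | 99.8% | 0.166 |
| Practice, GRIT only | case | 91.2% | 0.113 |

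With the residual method, 99.7% of resampled outcomes (both-arm mediator) and 87% (practice) were neither 0 nor 1. For practice, half of the resampled control values became non-zero, which the design rules out, and intervals were 0.166/0.113 = 1.47 times as wide as with the case bootstrap. For the both-arm mediator the two methods did not differ materially.

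**The case against.** Several points on the other side are sound.

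- **The mediator is exploratory.** Aim 2 names youth and caregiver self-regulation, and the analysis plan makes emotional regulation primary. That is so, and it limits the stakes. It does not make practice a suitable mediator.
- **The indirect effect is not wholly unidentified.** A reader might infer that, because no control practises, nothing can be estimated. The version evaluated under GRIT can be, on the strong assumptions in step 1.
- **A within-GRIT dose-response has the same confounding.** It does. The gain is that the result is then labelled as what it is and is not reported as a share of the randomised effect.
- **The collinearity may be harmless.** A reader might infer that the allowance of 1.4 must be exceeded. It is not exceeded if the CV is at least 1.12, and the plan does not tie 1.4 to each exploratory mediator.
- **The bootstrap variant and the mediation outcome scale are not stated.** A condensed article may leave both to a fuller document. A linear probability model, or resampling random effects and then drawing 0/1 outcomes, would be workable. A reader might therefore go too far in concluding that the method is undefined for a 0/1 outcome. The binary reading remains the likely one. The 30-day Timeline Followback amounts are a weak alternative: they are collected only after a positive report, so most youth would have zero, and added residuals could give negative amounts.
- **The primary mediators.** A reader might infer that all intervals for Aim 2 lack a valid basis. The documents do not support this: emotional regulation is measured in both arms on a near-continuous scale ("Total scores range from 18 to 90"), and simulated coverage for such a mediator was close to nominal. That simulation used a linear outcome model, so it does not vouch for a logistic one.

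**Conclusion.** The concern about practice holds. The article confines the means of practising to GRIT and yet lists practice beside mediators that vary in both arms. An indirect effect through it would combine assignment with self-selected adherence. This rests on reading practice as zero in controls, which follows from where the device, app, coaching and competition are provided. The precision cost depends on an unknown CV: the VIF is 3.0 at CV 0.5 and 1.22 at CV 1.5, with 1.4 reached at 1.12.

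The bootstrap point holds only as a mismatch between the named method, in its plain form, and the dichotomised outcome that the plan implies. It is not shown that intervals for the primary mediators are invalid, nor that a case bootstrap would improve their coverage. The primary efficacy analysis is unaffected by either point.

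**What to change.** 1. Remove HRV-biofeedback practice from the list of exploratory mediators. Report it as a dose-response within the GRIT arm, labelled non-randomised and open to confounding by adherence. Sleep, nutrition, physical activity and HRV itself can stay.
2. Replace the residual-based bootstrap for effects on dichotomised use with either a case bootstrap that resamples whole dyads within arm, or a parametric bootstrap that draws 0/1 outcomes from the fitted model. If a variant of the latter kind is already intended, or if the mediation outcome is not the dichotomised one, say so.

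The cost is one exploratory mediator, a change of wording and some computing time. Nothing changes in data collection, sample size or the primary analysis.
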